#### **Benefits to society:**

This study should improve knowledge of the effects of early plasma transfusion on patients in hemorrhagic shock and expand the indications for FLYP by bringing this treatment to the civilian population with the specific indication of trauma-induced hemorrhage.

#### **Known risks and constraints**

There are no known risks specific to the use of FLYP. The effect of cryodessication on the concentration of coagulation factors is a parameter that is monitored during manufacturing. The observational study on the use of FLYP in OPEX and certain exceptional situations, conducted since 2010 by the CTSA, has proven its tolerance and effectiveness.

In sporadic cases, transfusion of FFP may result in allergic reactions or respiratory complications (TACO).

It is necessary to observe whether the same clinical events occur with FLYP, knowing that its manufacturing method reduces this risk, as pooling minimizes the risk of immunological intolerance.

### **1.4 FLYP transfusion strategy**

Treatment of traumatic coagulopathy is based primarily on the provision of plasma coagulation factors and platelets.

FLYP has all the qualities of therapeutic plasma. It can be reconstituted in less than six minutes. It is universally used for ABO blood groups and can be stored at room temperature. Its sophisticated galenic form should be reserved for situations where significant logistical difficulties (impossible to ensure a negative cold chain or for extreme emergency situations where therapeutic plasma must be supplied without delay).

FLYP transfusion is recommended only in cases of severe coagulopathy with the collapse of all coagulation factors, acute bleeding with global coagulation factor deficiency, and complex coagulation factor deficiency when specific coagulation fractions are not available.

As a general rule, the transfusion should be performed rapidly (210 ml in 5 to 30 minutes) but should always be adapted according to the patient's clinical parameters. During prehospital management, a maximum of four units of FLYP will be administered per patient (dose recommended by the CTSA) depending on the patient's tolerance. The speed of administration will be 5 to 15 minutes per unit in this context.

## **1.5 Human subjects: Requirement for Emergency Research**

The research will be conducted following the trial protocol, the Good Clinical Practices (GCP), and the legislative and regulatory processes.

The CTSA's production of FLYP units complies with the rules established by the Good Transfusion Practices and the Good Manufacturing Practices applied to injectable products, Lifesaving Blood Products, and sterile products. It should be noted that the ANSM regularly inspects the CTSA in this context.

Each investigator agrees to provide free access to all source data required by the sponsor's monitor, persons conducting audits, and members of the CCP (Ethics Committee) or competent authorities.

The investigators, persons in charge of quality control, monitors, clinical research assistants, auditors and all persons called upon to collaborate in the trials, will respect legislative and regulatory recommendations, in particular, articles L. 1121-3 and R-5121-13 of the public health code, and will take all the necessary precautions to ensure the confidentiality of the information relating to the patient and the medicinal-trial products.

## **1.6 Study population.**

The study population consisted of adult patients with a hemorrhagic shock of traumatic origin managed by a prehospital medical team.

FLYP has been used for many years in traumatic contexts in the military environment. The population studied is justified by its belonging to civilian society, whose epidemiological profile is different from the military environment and deserves to be explored.

# **2 OBJECTIVES**

## **2.1 Main objective**

To show the effectiveness of FLYP administered prehospital during the management of hemorrhagic shock of traumatic origin, on the occurrence or treatment of post-traumatic coagulopathy.

## **2.2 Secondary objectives**

- Feasibility of FLYP administration in the prehospital setting
- Show that FLYP improves fibrinogen levels
- To show that the contribution of FLYP decreases the transfusion needs (RBC, plasma, coagulation factors, platelets)
- To show that the contribution of FLYP decreases the length of stay in intensive care
- Compare mortality between the two groups until Day-30

# **3 DESIGN**

## **3.1 Outcome variables**

### **Primary endpoint:**

- The primary endpoint is the international normalized ratio (INR) at hospital arrival.

### **Secondary endpoints:**

- The delta-INR value between the prehospital INR and the INR at hospital arrival. The Point of Care Device Coaguchek® will measure these two INR values
- Listing of technical and logistical difficulties encountered before, during, and after the administration of FLYP.
- The change in fibrinogen level between hospital admission and prehospital setting. The number of RBC units, platelet units, fibrinogen, plasma units, and quantity of coagulation factors administered during the first 24 and 48 hours.
- Length of stay in intensive care
- Length of hospitalization
- 30-days survival.

## **3.2 Methods**

### **3.2.1 Study design**

This trial is a multicenter, randomized, controlled, open-label pragmatic study.

### **3.2.2 Randomization**

Randomization assigns either the PLYO treatment combined with the usual treatment or the usual treatment alone.

CTSA randomizes study treatments in blocks of 2 boxes (one with PLYO, one without).

The treatment boxes are numbered in ascending order from 1 to 140.

The CTSA and the EFS will distribute the numbered boxes to the prehospital investigating centers as they are included (at the request of the centers) and by ascending order from 1 to 140. Therefore, only one package will be available in each ALS vehicle at the time of patient management.

The randomization list will be maintained by CTSA and SSA.

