### 3.8 Open-label

A blinded study cannot be performed because of the difficulties of manufacturing a placebo.

The study is therefore conducted in an open-label setting.

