#### **5.5 Practical procedures for accounting, storage, and delivery of experimental treatments within the investigating centers**

The experimental treatments are packaged and supplied by the CTSA. They will be distributed in batches of 2 (1 FLYP and one normal saline), either by the CTSA for the BSPP or by the regional Etablissement Français du Sang-EFS (tripartite agreement between the CTSA, the regional EFS, and the recruiting center) for the other prehospital investigating centers.

Study treatments will be stored and accounted for at each center. A copy of the detailed delivery note (date of shipment, lot number, quantity, expiry date) of the CTSA shipments will be kept there (Appendix 2). In these centers, these treatments will be stored in the in-house pharmacies under the same conditions as the other treatments routinely used in the prehospital setting but in a space specifically dedicated to the study.

Only one experimental treatment (bag containing FLYP or not) will be made available to the prehospital team in the AR or in the SMUR.

This treatment will be taken out of its packaging only when it is used.

As soon as the physician comes back from the intervention, he must return all the study elements to the center's manager.

No vial of FLYP from an opened batch shall be present in any AR/SMUR.

Unused, expired or unused FLYP units will be redirected to the CTSA.

Any FLYP that has not expired but is not usable due to improper storage conditions or any other reason must also be returned to the CTSA (with details of nonconformities) for inspection.

Suppose the FLYP is destroyed by the user (degradation without the possibility of a return to the CTSA) or in case of loss. In that case, the delivery slip will be returned to the CTSA with the mention destruction or loss of product at the level of the batch number, a duplicate will be kept at the concerned recruiting center.

Used and empty bottles will be thrown away (Incineration of hospital waste - DASRI).

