## 1611 **16.4   Randomization**

- 1612                   ▪   Randomization assigns either the FLYP treatment combined with the usual treatment or the
- 1613                   usual treatment alone.
- 1614                   ▪   CTSA randomizes study treatments in blocks of 2 boxes (one with FLYP, one without).

- 1615                   ▪ The treatment boxes are numbered in ascending order from 1 to 140.
- 1616                   ▪ The CTSA and the EFS will distribute the numbered boxes to the prehospital investigating
- 1617                   centers as they are included (at the request of the centers) and by ascending order from 1 to 140.
- 1618                   Only one pack will be available in each ALS vehicle at the time of patient management.
- 1619                   ▪ The randomization list will be maintained by CTSA and SSA.

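### Fixed blocks of two, shipped as one box of each arm in an open-label trial, let anyone who knows a pair's first box deduce its second

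*Combined protocol and SAP*

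**What the plan says.** Protocol 3.2.2 fixes the block size at two: "CTSA randomizes study treatments in blocks of 2 boxes (one with PLYO, one without"). SAP 16.4 says the same: "CTSA randomizes study treatments in blocks of 2 boxes (one with FLYP, one without"). On numbering, "The treatment boxes are numbered in ascending order from 1 to 140", and the boxes go to centres at their request "by ascending order from 1 to 140". Protocol 5.5 sets the delivery unit: "They will be distributed in batches of 2 (1 FLYP and one normal saline"). Ascending distribution in batches of two implies that a centre receives both boxes of a pair.

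There is no blinding (Protocol 3.8): "The study is therefore conducted in an open-label setting".

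The stated safeguards are these:

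- One box per vehicle: "Only one experimental treatment (bag containing FLYP or not) will be made available to the prehospital team in the AR or in the SMUR" (Protocol 5.5; also 3.2.2 and SAP 16.4).
- The package is opened only at use, and stock is held in the centre's pharmacy (Protocol 5.5).
- The randomization list is held by CTSA and SSA (Protocol 3.2.2, SAP 16.4).

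The documents mention no varying or concealed block size and no central allocation after enrolment. They do not say that the two kinds of package look alike, or that the second box of a pair is kept from staff who know the first.

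**The concern.** With blocks of two, opening one box reveals the other. Open-label use makes the first box's content visible, and paired delivery places the second box at the same centre. Nobody has to infer the block size, because it is printed in the protocol.

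A clinician who knows the arm of the next box can, even without intent, be readier or slower to enrol a given patient. The arms would then differ in severity before treatment starts. The primary endpoint is arrival INR rather than the change from the prehospital value, and the primary test is an unadjusted Mann-Whitney comparison. Adjustment is only to be considered if initial characteristics turn out unbalanced (Protocol 8.1, SAP Analysis methods). A severity difference created by selection would therefore enter the primary result directly.

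**Working it through.** **Inputs.** Block size 2 (Protocol 3.2.2, SAP 16.4); 140 boxes, so 70 pairs; SD 0.4 and difference 0.3 (Protocol 8.2, SAP 16.5). The plan gives no figure for predictability. Its sample size is reproduced closely: 2 × (1.96 + 0.84)² × (0.4/0.3)² = 27.9, so 28 per group (29 with a t-test) against the stated 30. That figure does not depend on block size. It is shown only because the SD is reused below.

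**Predictability.** Suppose all earlier allocations at the centre are known. For a fixed block with m boxes per arm, the share of allocations that are fully determined is 1/(m + 1). For m = 1, the first box is guessed with probability 0.5 and the second with certainty, so the best-guess rate is (0.5 + 1)/2 = 0.75. Enumerating the sequences for larger blocks gives:

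| Scheme | Determined | Of 140 | Best guess correct | Of 140 |
|---|---|---|---|---|
| Fixed 2 (plan) | 50% | 70 | 75% | 105 |
| Fixed 4 | 33% | 46.7 | 70.8% | 99.2 |
| Fixed 6 | 25% | 35 | 68.3% | 95.7 |
| Random 4 and 6, sizes concealed | not knowable with certainty while the sizes stay hidden | – | about 69% (simulated) | – |

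Chance is 50%. The gain from larger, concealed blocks is mainly the loss of certainty; the guessing rate falls only modestly.

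**What selection could do (illustration only).** The documents give no size for a selection effect, so the following is assumed: SD 0.4 for all 140 patients, no treatment effect, and a fraction k of second boxes known to the enrolling physician. When the next box is known, enrolment shifts expected INR by x in FLYP's favour (lower if the box is FLYP, higher if it is saline). Half of each arm comes from second boxes, so the arm means move by −xk/2 and +xk/2, and the bias is xk. The standard error is 0.4 × √(2/70) = 0.0676. Type I error is approximately Φ(−1.96 + xk/0.0676) + Φ(−1.96 − xk/0.0676):

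| x (INR) | k = 1 | k = 1/2 | k = 1/4 |
|---|---|---|---|
| 0.05 | 0.115 | 0.066 | 0.054 |
| 0.10 | 0.316 | 0.115 | 0.066 |
| 0.15 | 0.602 | 0.199 | 0.086 |

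Simulating the planned Mann-Whitney test (2000 trials per design) at k = 1 gives 0.12, 0.30 and 0.56 for the three values of x, in line with the formula. If concealed random blocks of 4 and 6 are used and the physician guesses the arm that is behind, with the same shift x, the values are 0.09, 0.19 and 0.36.

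**Precision of a first-box analysis.** Restricting to first-used boxes leaves about 35 per arm. The standard error becomes 0.4 × √(2/35) = 0.0956, and the 95% half-width rises from 0.13 (70 per arm) to 0.19.

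**The case against.** The strongest reply is that determinable is not the same as known. Each vehicle carries one box, packages stay closed until use, and stock is kept in the pharmacy. A team in another vehicle need not know what the first box of its pair held. This stands, and it makes 70 of 140 and 75% upper bounds. It does not remove the problem. One box per vehicle stops a team choosing between boxes but does not hide the arm of the next one. Treatments are also stored and accounted for at the centre, where the study elements are returned after use.

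A reader might infer more than the documents support in three ways:

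- That small centres with one or two teams would always know. No section gives vehicle or team counts, and the return of study elements informs the centre's manager, who is not said to enrol patients or to tell other teams.
- That enrolment is discretionary. Protocol 4.1 sets numerical criteria, and 4.7 says that participation will be offered to selected patients who meet them. The investigator-decision clause in 4.7 is an emergency-consent provision, not freedom to choose among eligible patients. Some room remains, since the criterion may be met at any time in prehospital care.
- That the plan has no protection at all. Prehospital INR is taken before study treatment and described by arm, adjusted analysis is foreseen, delta-INR is a secondary endpoint, and screened numbers are reported per centre. These could expose or soften an imbalance, but they do not prevent selection.

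It can also be said that the remedy comes late. The protocol and SAP are dated May 27, 2019 and the study was extended to September 2019, so few boxes may remain unissued; the documents give no count. This is fair. It is why the analysis step below matters more than the new list.

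**Conclusion.** The concern holds in a limited form. Fixed blocks of two, one-plus-one delivery and open-label use together make the second allocation of every pair determinable by staff who know the first: up to 70 of 140 allocations, and up to 105 of 140 guessed correctly. The stated safeguards reduce this but do not remove it.

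The stronger conclusions, that half the allocations were actually known to enrolling physicians or that the result is biased, are not supported. The documents do not show who knew what, nor that any selection took place. The type I error figures rest on assumed values of x and k. If a quarter of second boxes or fewer are known, inflation is small over the range shown (at most about 0.09). If all are known, it is serious from a shift of about 0.10.

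**What to change.** **1. Boxes not yet issued, if any.** Replace the fixed blocks of two with a separate list for each centre, using randomly varying blocks of 4 and 6. Keep the sizes from the centres and out of the protocol. Ship in list order, in deliveries that need not hold one box of each arm. Amend Protocol 3.2.2 and 5.5 and SAP 16.4 to match. The cost is re-labelling the remaining boxes, slightly uneven FLYP stock and a within-centre imbalance of up to 3. That cap holds only with a list per centre; if a single 1 to 140 list is split across centres, blocks are broken up and the cap fails.

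**2. Pairs already issued.** Report prehospital INR and shock index by arm, separately for first-used and second-used boxes. Both are already planned baseline items. A severity difference confined to second-used boxes would point to selection; its absence would be reassuring but not proof.

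**3. Sensitivity analysis.** Add to the SAP a comparison of arrival INR restricted to first-used boxes, stating its lower precision. Note also that prehospital point-of-care INR may be missing for patients enrolled before the January 2017 amendment that introduced the device.

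Steps 2 and 3 need only the box number and order of use alongside data already planned for collection. They cost one descriptive table and one extra analysis.

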## **3.3 Study timelines**

The study comprises two phases of investigation: the prehospital phase and the hospital phase.

### **3.3.1 Prehospital phase**

This phase is performed by a prehospital investigator after verification of inclusion and non-inclusion criteria. During this phase, no fibrinogen or other coagulation factors, other than FLYP

Before the administration of the experimental treatment, the management of a patient will be :

- Stop the bleeding (tourniquet or hemostatic dressing or pressure point if necessary)
  - Measure clinical and biological parameters (HR, BP, SpO2, hemoglobin level,...)
  - Take a sample (1 drop of blood) to measure the prehospital PT/INR with the Coaguchek®.
  - If possible, take a venous sample before any drug administration, using two blue tubes (PT, aPTT, fibrinogen, coagulation factors) and two purple tubes (blood group, platelets, etc.).
- Particular attention must be applied to the filling of the tubes, which must be COMPLETE so that the results of the analyses can be interpreted.

- Ventilatory support with oxygen supply (high concentration mask or orotracheal intubation and mechanical ventilation)
- **For the FLYP (+) group: Administration of FLYP, up to 4 units (800ml)**  
Plasma units are reconstituted as needed.  
Any connected and opened bottles are left with the patient.
- **For the FLYP (-) group: Administration of saline solution,** as much as necessary to reach the goals recommended by the guidelines.

Then, for the two groups, according to the patient's clinical parameters:

- Use of amines, and tranexamic acid
- The dosage of crystalloids and the use of amines should make it possible to reach the goals recommended by the guidelines.

### 3.3.2 Hospital phase

#### At hospital arrival:

- Biological samples ( PT, aPTT., fibrinogen, CRP, and coagulation factors)
- Administration of the usual treatments.
- Follow-up by the hospital-based investigator for 30 days (
  - patient status (alive, deceased)
  - date of discharge from the intensive care unit and the hospital
  - follow-up of AEs, SAEs
  - Hemostasis test results collection.

All procedures performed during this phase will conform with the standard practices in use in each hospital.

Biological samples will not be stored after their usual processing.

### 3.3.3 Standard Operating Procedure for the biological tubes:

Prehospital blood samples are part of the usual diagnostic process of post-traumatic coagulopathy.

Prehospital blood samples will be collected prior to administration of the study treatment and dispatched to the hospital laboratory through each hospital's dedicated circuit.

The prehospital physician will write on the tube of collected blood sample :

- The patient's first and last name
- The patient's inclusion number
- The name of the prehospital center
- Date and time of sampling

A "patient label" (with name, first name, date of birth, date of hospital admission) will be created when the patient arrives in the hospital. This label will be fixed on the tube to facilitate the procedures of the laboratory technicians.

The prehospital physician will complete the blood test request sheet and will precise the indication "SAMPLE COLLECTED BEFORE ANY PLASMA TRANSFUSION."

**Samples collected after hospital admission** will follow the same process. But the blood sample analysis request sheet will be filled out by the Senior Physician in charge of the hospital admission unit. The request sheet will be precise with the indication: "POST FLYP TRANSFUSION."

The prehospital physician who transported the patient to the hospital makes the final check with the admission unit to ensure that the laboratory request forms have been completed correctly and that the tubes have been correctly labeled and placed in the dedicated container (plastic bag).

Particular attention should be paid to identifying samples and the storage of samples corresponding to the coagulation factors. Care should be taken to ensure that the time for analysis and determination of coagulation factors is less than 6 hours. Samples should be stored at room temperature.

The biological samples directly related to the study will not be stored after their analysis.

### 3.3.4 Synopsis of the study

[figure not shown]

T, Time; PT, Prothrombin time level; INR, International normalized ratio; FLYP, French lyophilized plasma.

### 3.3.5 Research timeline

|                                                                 | Phase
Prehospital | Hospital phase |           |              |
|-----------------------------------------------------------------|----------------------|----------------|-----------|--------------|
|                                                                 |                      | Admission      | Follow-up | End of study |
| Consent or follow-on consent                                    | X                    | X              | X         | X            |
| Background                                                      | X                    | X              |           |              |
| Verification of inclusion, non-inclusion and exclusion criteria | X                    | X              | X         | X            |
| Clinical examination                                            | X                    | X              | X         | X            |
| Biology:                                                        |                      |                |           |              |
| • PT/INR                                                        | X                    | X              |           |              |
| • Prehospital INR                                               | X                    |                |           |              |
| • TCA and fibrinogen                                            | X                    | X              |           |              |
| • platelets                                                     | X                    | X              |           |              |
| • CRP                                                           | X                    | X              |           |              |

|                |                                                                 |   |   |   |
|----------------|-----------------------------------------------------------------|---|---|---|
| • Blood Group  |                                                                 |   |   |   |
| Randomization  | Up to 4 FLYP + reference
TREATMENT Or reference
Treatment |   |   |   |
| Adverse events | X                                                               | X | X | X |

